#### Data analysis

Interim data analysis will not be carried out. Continuous data will be presented as means with SD or as median with interquartile range (IQR) depending on the nature of data. Categorical data will be presented as counts with percentages. Differences in demographic data and outcome measures between groups will be compared using chi-square for categorical data and Student’s *t*-test (parametric data) or Wilcoxon signed rank test (non-parametric data) for continuous data.

An intention-to-treat analysis will be conducted for the primary outcome. A per-protocol analysis will be conducted to test the non-adherence to the protocol, and patients who do not comply with the protocol will be excluded. Primary outcome will be analysed with a mixed effect model adjusted for fracture location, smoking habits and dislocation (the strata in the block randomization) to account for imbalance in baseline covariates and to improve the power of the treatment effect.

Subgroup analyses for the duration of non-union (< 6 months vs. > 6 months), patients with/without deformity based on the preoperative measurements of HLR and DCA will be performed. It will be clarified if post hoc analyses are carried out. For missing data in an outcome measure, multiple imputation analysis with the covariates: age, smoking, fracture location, dislocation > / < mm and duration of non-union will be conducted to minimize bias of nonresponse. Applied level of significance for all statistical analyses is *P* < 0.05. The statistical analyses will be performed using computerized statistical software.

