## Subjects

A total of 88 patients with scaphoid delayed/non-union are randomized to either:Group A – Arthroscopic assisted C chips graft reconstruction (intervention group), *n* = 44Group O – Open C graft reconstruction (control group), *n* = 44

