## Randomization

Based on the sample size calculation, a total number of 88 patients will be allocated into two groups of equal size.Group A – Arthroscopic assisted C chips graft reconstruction (intervention group), *N* = 44.Group O – Open C graft reconstruction (control group), *N* = 44.

The randomization is done in the outpatient clinic and the patients will be informed about the operative treatment. The randomization is done using an irreversible application in Research Electronic Data Capture (REDCap). Patients will be allocated in a 1:1 ratio by block randomization, stratified for proximal pole fracture (yes /no), dislocation (> / < 2 mm) and smoking (yes/ no). An independent statistician generated the randomization sequence for REDCap, and thus the allocation is concealed to the research staff and physicians.

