### Statistics

#### Sample size calculation

The sample size calculation was performed with an expected mean time to union of 56 days and a SD of 30 days in Group A and 77 days and SD on 40 days in group B. The sample size required in each group to provide 80% power to detect a mean 3 weeks difference [13], with two-sided alpha on 0.05, was 36 patients in each group. Considering dropouts and loss to follow-up with a rate of 20% the final number of patients needed in total for this study is 88 patients.

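### The plan names a paired test, the Wilcoxon signed rank test, for non-parametric comparison of two independent randomised groups

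*Protocol article*

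**What the plan says.** In the protocol article, the Data analysis section gives a single rule for comparing the arms: "Differences in demographic data and outcome measures between groups will be compared using chi-square for categorical data", with Student's t-test for continuous data treated as parametric and otherwise the "Wilcoxon signed rank test (non-parametric data) for continuous data". The rule covers baseline characteristics as well as outcomes.

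The groups are formed by ordinary parallel allocation. Under Subjects: "A total of 88 patients with scaphoid delayed/non-union are randomized to either" of two groups of 44. Under Randomization: "Patients will be allocated in a 1:1 ratio by block randomization", stratified by proximal pole fracture, dislocation and smoking.

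The primary outcome is handled separately, again under Data analysis: "Primary outcome will be analysed with a mixed effect model adjusted for fracture location, smoking habits and dislocation".

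No section names a rank-sum or Mann-Whitney test, and none reserves the signed rank test for change within a patient.

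**The concern.** The signed rank test ranks the absolute values of within-pair differences, so it needs a defined partner for every observation. A patient in the arthroscopic arm has no partner in the open arm. The sentence is expressly about differences between groups, so the named test does not fit the comparison it is given.

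At stake is the pre-specified analysis of continuous secondary outcomes on the non-parametric branch. For Q-DASH, which the protocol calls its primary functional outcome, the article gives no other between-group method. The same holds for VAS pain, donor-site pain, range of motion, grip strength and key pinch. An analyst who follows the text either gets no result or gets one that another analyst cannot reproduce. An analyst who switches to a different test does so after the fact, in a trial whose patients and surgeons know the allocation.

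**Working it through.** The point concerns the choice of test and rests on no figure in the plan, so there is no stated number to reproduce. The check has four steps.

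**1. Does the design supply pairs?** No. Each of the 88 patients is randomised to one arm only. Strata and blocks balance the arms, but they do not match individual patients, and no section defines a pairing. Within-patient contrasts do exist under Secondary outcomes (affected against unaffected wrist; preoperative against follow-up scaphoid measurements), but the Data analysis section does not assign the signed rank test to them.

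**2. Will the analysed arms be equal in size?** Probably not.
- Patients are randomised in the outpatient clinic, but the Enrolment section has some excluded during surgery, when no punctate bleeding is seen.
- The Sample size calculation allows for 20% dropout. Assume exactly 44 per arm and independent dropout at that rate. The number remaining in each arm is then Binomial(44, 0.8), with mean 44 × 0.8 = 35.2 and SD √(44 × 0.8 × 0.2) = 2.65. The chance of equal numbers is Σ P(k)² ≈ 1/(2√π × 2.65) ≈ 0.11. At 10% dropout the same sum is 0.14, and at 5% it is 0.20.

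With unequal arms the test has no value. A trial call with 43 against 44 observations returned an error.

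**3. If the arms are equal, is the result defined?** With 44 per arm there are 44! ≈ 2.7 × 10^54 ways to pair the patients, and the plan selects none. To illustrate, one data set was simulated from the only means and SDs that the article gives, those for time to union. The arthroscopic arm has an "expected mean time to union of 56 days and a SD of 30 days in Group A". For the open arm, the Sample size calculation gives "77 days and SD on 40 days in group B". A gamma distribution was assumed, with shape (mean/SD)² and scale SD²/mean:
- Arthroscopic: shape (56/30)² = 3.48, scale 900/56 = 16.07.
- Open: shape (77/40)² = 3.71, scale 1600/77 = 20.78.

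| Test on the same 44 + 44 values | p-value |
|---|---|
| Rank-sum (Mann-Whitney) | 6.1e-5 |
| Signed rank, 2,000 random pairings: minimum | 5.0e-7 |
| 2.5th percentile | 9.7e-6 |
| median | 1.5e-4 |
| 97.5th percentile | 7.4e-4 |
| maximum | 1.6e-3 |

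The largest is about 3,100 times the smallest (1.55e-3 / 5.00e-7). All lie below 0.05, so the pairing did not change significance in this data set. It changed only the reported p-value.

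**4. Does arbitrary pairing distort the error rates?** Under the same gamma assumption, 4,000 simulated trials were run with 36 per arm, the number per group before the dropout allowance, at two-sided 0.05:

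| | Signed rank, arbitrary pairing | Rank-sum |
|---|---|---|
| Type I error (both arms 77, SD 40) | 0.052 | 0.053 |
| Power (56, SD 30 against 77, SD 40) | 0.67 | 0.68 |

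The Monte Carlo standard error is about √(0.05 × 0.95 / 4000) = 0.003 for the first row and √(0.67 × 0.33 / 4000) = 0.007 for the second. The two tests do not differ beyond simulation error.

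Time to union serves here only as a convenient skewed variable. The rule in question does not govern the primary analysis.

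**The case against.** The strongest reply is that this is a slip between two tests with nearly the same name. The sentence sets the test beside Student's t-test for group comparison, and a competent analyst would run the rank-sum test without hesitation. Unequal arms would also expose the error at once, because software would refuse the calculation. That is persuasive on severity. It does not remove the error: a pre-specified method should be executable as written, and the text names the wrong one.

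A second reply is that the planned multiple imputation would fill in missing outcomes and restore equal arms. It would not replace patients excluded at surgery. Where it did restore equality, the pairing would still be arbitrary.

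A third is that such detail belongs in an analysis plan that is not shown. That would excuse silence, but the article is not silent.

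Two stronger readings are tempting, and the documents support neither.
- A reader might infer that a wrong test means false positives or lost power. Step 4 shows neither.
- A reader might infer that most secondary results are affected. The article gives no distribution for any secondary outcome, so how often the non-parametric branch would be used is unknown. Union rate, complications, reoperations and the yes/no satisfaction item are categorical and go to chi-square. The seven-level satisfaction item is ordinal, and the text does not place it under the rule for continuous data.

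**Conclusion.** The point holds as an error of specification with limited reach. A paired test is assigned to unpaired groups. As written it cannot be computed with unequal arms, and with equal arms it has no unique value.

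It affects continuous baseline variables, where the consequence is small, and any continuous secondary outcome judged non-normal. It leaves the primary comparison of time to union untouched. There is no bias to quantify, no inflated error rate was found, and the sample size does not change.

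That the test is paired and the arms are not follows from the text alone. The spread of p-values and the error rates rest on the assumed gamma distribution, and the spread also on a single simulated data set. The chance of equal arms rests on independent dropout at the assumed rates.

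**What to change.** In the Data analysis section, replace the signed rank test with the Wilcoxon rank-sum (Mann-Whitney) test for between-group comparison of non-parametric continuous data. If within-patient comparisons are planned, say so and name the signed rank test for those only.

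This is a one-line correction. It needs no new data and no change to the sample size, and it should be recorded before the analysis begins.

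A version stratified by the randomisation factors, or a Hodges-Lehmann difference with its confidence interval, is optional and not needed to correct the error. Three binary factors give 2 × 2 × 2 = 8 strata, on average 88 / 8 = 11 patients each. Stratifying only the rank test would also leave it out of step with the unstratified t-test named in the same sentence.

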## Physiotherapy and rehabilitation

Rehabilitation will be identical between the groups. Stitches are removed 2 weeks postoperatively. Patients will be provided a thumb/wrist splint for 2 weeks, followed by the application of removable orthosis for another 4 weeks allowing the beginning of light non-weight-bearing exercises. The wrist will be allowed mobilization without restrictions if union is established on a postoperative CT scan and with the absence of scaphoid tenderness on the clinical examination. Return to work will be accepted when the union is established.

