## Protocol violations and patient drop-out

The patients evaluated for inclusion will be reported in a consort diagram (Fig. 3). The statistical analysis will be conducted on an intention-to-treat basis. Outcome scores will be analysed according to the initial study group assignment regardless of possible cross-over. If crossover does occur, a secondary per-protocol analysis will be conducted.

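### The article states two different per-protocol rules, and the broader one could select patients on time to union if breaches of restrictions that last until union led to exclusion

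*Protocol article*

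**What the plan says.** Two sections of the Protocol article set a per-protocol rule.

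- **Protocol violations and patient drop-out.** Patients are analysed as assigned: "Outcome scores will be analysed according to the initial study group assignment regardless of possible cross-over". The per-protocol analysis is conditional and secondary: "If crossover does occur, a secondary per-protocol analysis will be conducted".
- **Statistics, Data analysis.** "An intention-to-treat analysis will be conducted for the primary outcome". Then, with no condition attached: "A per-protocol analysis will be conducted to test the non-adherence to the protocol, and patients who do not comply with the protocol will be excluded".

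Two other sections show which obligations last until union.

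- **Physiotherapy and rehabilitation.** "The wrist will be allowed mobilization without restrictions if union is established on a postoperative CT scan", provided scaphoid tenderness is also absent. For work: "Return to work will be accepted when the union is established". The splint (2 weeks) and the removable orthosis (4 further weeks) have fixed durations for everyone.
- **Primary outcome.** CT is repeated every 2 weeks from week 6 to week 16, with a scan at week 24 if union has not been reached. The Discussion counts up to 7 scheduled scans for patients with prolonged union time.

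**The concern.** The two rules differ in when the analysis is run and in who is left out. Without crossover, one section calls for no per-protocol analysis and the other requires one. With crossover, one points to the operation received, while the other covers any non-compliance. Two written rules leave room to choose the population after the data are seen.

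The broader rule carries a further risk. Several obligations end only when the primary outcome occurs, so the time at risk of a breach grows with time to union. If a breach of those obligations led to exclusion, slow healers would be removed more often, even if compliance had no influence on healing. Data analysis gives the purpose as "A per-protocol analysis will be conducted to test the non-adherence to the protocol". A reader could therefore take a gap between the per-protocol and intention-to-treat estimates for an effect of adherence when it came from selection.

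**Working it through.** **1. The rules side by side**

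| | Protocol violations and patient drop-out | Data analysis |
|---|---|---|
| Run when | Only if crossover occurs | Always |
| Left out | Not spelled out; crossover is the only deviation named | Every patient not complying with the protocol |
| Status | Secondary | Not stated; follows the intention-to-treat sentence for the primary outcome |

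The conflict needs no arithmetic.

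**2. Exposure to a breach**

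Scans fall at weeks 6, 8, 10, 12, 14, 16 and 24, which is 7 and agrees with the Discussion. A patient united at week 6 has one scan and is then released from the work limit. A patient not united at week 16 has had six scans, has one more to come, and stays under the work and mobilisation limits beyond that point. All patients share the first 6 weeks, so the outcome-dependent exposure is what comes after week 6.

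**3. Illustration of size, closed form**

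Inputs from Sample size calculation: mean 56 days, SD 30 (Group A); mean 77 days, SD 40 (called group B there, taken here as Group O). Planned difference: 77 − 56 = 21 days.

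Assumptions not in the article: gamma-distributed times to union; a constant breach rate from surgery until union, equal in both arms and unrelated to healing; every breach excludes.

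With mean m and SD s, shape k = (m/s)² and rate r = m/s². With h = weekly rate/7 per day:

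- proportion kept = (r/(r+h))^k
- mean among those kept = k/(r+h)

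Group A: k = (56/30)² = 3.484, r = 56/900 = 0.06222. Group O: k = (77/40)² = 3.706, r = 77/1600 = 0.04813.

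At 3% per week, h = 0.03/7 = 0.00429. Group A: 3.484/0.06651 = 52.4 days. Group O: 3.706/0.05241 = 70.7 days.

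| Assumed weekly rate | Kept A / O | Mean A / O (days) | Difference (days) |
|---|---|---|---|
| 0 | 100% / 100% | 56 / 77 | 21 |
| 2% | 86% / 81% | 53.5 / 72.7 | 19.1 (from unrounded means) |
| 3% | 79% / 73% | 52.4 / 70.7 | 18.3 |
| 5% | 68% / 60% | 50.2 / 67.0 | 16.8 |

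At 5% the loss is 21 − 16.8 = 4.2 days, or 4.2/21 = 20%.

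**4. Check on the CT schedule**

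A simulation used the same gamma times, read at the scheduled scans (later unions set to week 24), with breaches possible from week 2 until union is declared. Nobody is released before week 6. The full-cohort difference is 88.1 − 67.0 = 21.1 days.

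| Assumed weekly rate | Excluded A / O | Per-protocol difference (days) |
|---|---|---|
| 1% | 7.2% / 10.0% | 19.9 |
| 2% | 13.9% / 18.7% | 18.8 |
| 5% | 30.7% / 39.3% | 15.6 |

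The direction is the same as in step 3.

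**5. No true difference**

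On the same schedule, with both arms at mean 77 and SD 40, equal breach rates give no spurious difference. Unequal rates do: 1% against 2% gives 2.4 days, and 2% against 5% gives 6.4 days. The arm with the higher breach rate looks faster. Under Blinding, patients, surgeons and physiotherapists know the allocation, so unequal rates cannot be ruled out.

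**The case against.** The strongest reply is that the article never names early return to work, early wrist use or a missed scan as a ground for exclusion. The only deviation that it links explicitly to a per-protocol analysis is crossover, and the sentence under Data analysis may be a short restatement of that rule. On that reading the trigger hardly matters, because without crossover the per-protocol and intention-to-treat sets coincide. A detailed definition of compliance may also sit in a full protocol or analysis plan that is not shown, and its absence from an article is no fault.

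Much of this stands. A reader might infer that the plan will remove slow healers; the text only permits it. A reader might also infer that a patient united at week 6 could scarcely breach anything. The fixed 6 weeks of splint and orthosis contradict that: at the constant rates of step 3, such a patient has a breach probability of 1 − exp(−0.18), about 16%, at 3% per week, and 1 − exp(−0.30), about 26%, at 5%. Missed scans are the weakest example. The drop-out section keeps a patient with the latest follow-up if a 6-week evaluation exists, Data analysis imputes missing outcomes, and no scan is scheduled between weeks 16 and 24. The breach rates are assumed, and the 20% loss requires about a third of Group A and 40% of Group O to be excluded.

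Two things remain. The conflict lies between two rules that the article itself states, so a later document that settled it would still leave one section wrong. And the words "patients who do not comply with the protocol will be excluded" carry no limit to the operation received.

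**Conclusion.** The two per-protocol rules conflict in trigger and in population and must be reconciled. Selection on the primary outcome is a conditional risk of the broader wording: it arises only if breaches of restrictions lasting until union are counted as non-compliance and lead to exclusion. Under the stated assumptions, equal weekly breach rates of 2% to 5% would shrink the 21-day difference to about 19.1 to 16.8 days. The CT-schedule version gives 18.8 to 15.6 days against 21.1.

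The documents do not support the stronger inference that the trial's main result is biased or that a false benefit is to be expected. Intention-to-treat remains the analysis of the primary outcome and is untouched. With equal breach rates the per-protocol estimate is only drawn towards no difference; a spurious difference needs unequal rates. The point concerns a secondary analysis, but it is worth correcting before data are seen.

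**What to change.** Put the same rule in Protocol violations and patient drop-out and in Data analysis. For example: the supportive per-protocol set consists of all randomised patients who received the operation to which they were allocated; the analysis is run whether or not crossover occurs; deviations after surgery from rehabilitation, work limits or CT visits are tabulated by arm and are not grounds for exclusion from this set. Drop the statement that the analysis tests non-adherence to the protocol, or limit it to adherence to the allocated operation.

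The cost is wording only. It needs the allocated and the performed operation for each patient, and it leaves patient management unchanged. The downside is that the per-protocol analysis would address only adherence to the allocated operation and say nothing about adherence to rehabilitation. Other definitions are possible, but any that uses conduct between surgery and union would have to deal with the dependence on the outcome shown above.

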## Background

A scaphoid fracture is the most common injury to the carpal bones. The incidence is 107–151/100.000 per year and fractures are predominantly sustained by males in their twenties [1]. Scaphoid non-union is defined as a lack of healing 6 months after injury and develops in 5–25% of cases after non-operative treatment [2, 3]. Delayed union is defined as incomplete healing 2–6 months after injury. However, some potential for a union probably exists, especially in nondisplaced fractures, otherwise this condition is associated with a transition into a persistent non-union [4]. The risk of non-union increases with delayed diagnosis and treatment, displaced fractures, proximal pole fractures, smoking, poor vascularity and advancing age [5–8].

The scaphoid is primarily covered with cartilage and has a retrograde blood supply. The dorsal branch of the radial artery accounts for 80% and a separate volar branch for 20% of the extramedullary blood supply. The proximal pole is only supplied by the intramedullary flow. Compromised blood supply can explain the potential of non-union and avascular necrosis of the proximal pole. The healing process can be complicated by volar angulation of the fracture leading to humpback deformity. This will disrupt carpal kinematics and result in lunate instability and dorsal intercalated segment instability (DISI). Untreated scaphoid non-union can lead to degenerative changes, called scaphoid non-union advanced collapse (SNAC), and irreversible impairment such as pain and altered hand function.

X-ray is commonly applied to evaluate the scaphoid, although CT scans are reportedly superior in terms of displacement, angulation and union [9]. Different measurements to describe the angulation and deformity of the scaphoid are suggested. The height length ratio (HLR) and dorsal cortical angle (DCA) (Fig. 1) are found to be the most reliable measurements [10, 11].

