## Inclusion criteria

Patients aged 18–68 years.A scaphoid fracture without healing 3–6 months since fracture (delayed union) for cases with either displacement > 1 mm or comminution and failed non-operative treatment.Scaphoid fracture without healing > 6 months since fracture (non-union) regardless of displacement, comminution and if previous non-operative treatment has been tried.ASA 1–3.

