## Enrolment

All Danish citizens aged 18–68 years with scaphoid delayed/non-union referred to the hand surgy unit, Herlev and Gentofte University Hospital, will be offered participation in the study. Other hand unit departments in the Capital Region of Denmark will forward their referrals to our department for inclusion. The physician will review the medical records and assess whether the patients fulfil the inclusion/exclusion criteria. If the patient is found eligible, they will receive oral and written information of the study (Fig. 2) and the possibility to bring a bystander for the preparation consultation. The patients will be given a minimum of 24 h deliberation period. At the preparation consultation with the primary investigator, the patient will once again receive oral and written information, and trial risks of the study, and subsequently the consent will be obtained. The patients will simultaneously be allocated to one of the treatment groups. Patients can withdraw their consent at any time. The Helsinki Declaration will be followed [25]. The informed consent will give the primary investigator access to information about sex, age, comorbidity, trauma, time from fracture to treatment, history of smoking, occupation, hand dominance, pain, ongoing workers’ compensation and insurance claim. Baseline range of motion, grip strength, Key-pinch strength, pain in rest and activity (VAS) and Q-DASH will be recorded (Fig. 2).

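### The primary time-to-union model adjusts only for the three randomisation strata and leaves out duration since fracture and age, giving up a little precision that costs almost nothing to recover

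*Protocol article*

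**What the plan says.** The Inclusion criteria admit patients by two routes that divide at 6 months from fracture. The first is "A scaphoid fracture without healing 3–6 months since fracture (delayed union) for cases with either displacement > 1 mm or comminution and failed non-operative treatment". The second is "Scaphoid fracture without healing > 6 months since fracture (non-union) regardless of displacement, comminution and if previous non-operative treatment has been tried".

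Under Randomization, allocation is "stratified for proximal pole fracture (yes /no), dislocation (> / < 2 mm) and smoking (yes/ no"). Under Data analysis, "Primary outcome will be analysed with a mixed effect model adjusted for fracture location, smoking habits and dislocation (the strata in the block randomization"); the same sentence gives the aims as dealing with baseline imbalance and raising power. Neither list contains duration or age.

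Both variables appear elsewhere in the protocol:
- Background: "The risk of non-union increases with delayed diagnosis and treatment, displaced fractures, proximal pole fractures, smoking, poor vascularity and advancing age".
- Enrolment: age is recorded, and so is "time from fracture to treatment, history of smoking, occupation".
- Data analysis: a subgroup analysis compares durations below and above 6 months, and the multiple imputation model includes both age and duration of non-union.

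**The concern.** The Background sentence names six kinds of risk factor. Displacement, proximal pole involvement and smoking enter the primary model. Delayed treatment and age do not, and no reason is given. If the adjustment is meant to deal with baseline imbalance, the three chosen factors are those that stratified blocks already keep roughly balanced. Duration and age are left to chance, so an adjustment has more to correct there.

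Two things are at stake. Any outcome variation explained by duration or age stays in the residual, which widens the confidence interval. And if the arms happen to differ in their mix of delayed unions and non-unions, the stated model cannot correct for it, while a covariate added after the imbalance is seen would be post hoc.

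**Working it through.** **Inputs from the protocol (Sample size calculation).** Means 56 and 77 days (difference 21), SDs 30 and 40, 80% power, two-sided alpha 0.05, 36 per group, 88 in total after a 20% allowance.

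**Inputs assumed, because the documents do not give them.** Share of delayed unions p = 0.2 to 0.5. Difference in mean time to union between the two routes, g = 7 to 21 days. The upper end of g equals the whole target treatment effect, so it is generous.

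**Step 1: the plan's own figure.** Root-mean-square SD = √((30² + 40²)/2) = √1250 = 35.4 days. Normal approximation: n = 2 × (1.960 + 0.842)² × 1250 / 21² = 44.5, so 45 per group two-sided. With 1.645 in place of 1.960, n = 35.1, so 36 per group. The stated 36 therefore matches a one-sided 0.05 test and not the two-sided test described. That is a separate matter; it is used here only to set the baseline power. The standard error is √(2500/n): 8.33 days at 36 per group and 7.54 days at 44. Two-sided power is 0.712 and 0.796.

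**Step 2: size of a chance imbalance.** SD of the difference in delayed-union share = √(2p(1−p)/n). The 95% range of the resulting shift in the treatment difference is ±1.96 × g × that SD. Example with n = 44, p = 0.3, g = 14: √(0.42/44) = 0.098, and 1.96 × 0.098 × 14 = 2.7 days.

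**Step 3: precision gained by adjusting for duration.** Share of variance explained R² = p(1−p)g²/1250. The adjusted SD is 35.4 × √(1−R²).

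| n per group | p | g (days) | 95% shift (days) | R² | Power unadjusted | Power adjusted |
|---|---|---|---|---|---|---|
| 36 | 0.2 | 7 | ±1.3 | 0.006 | 0.712 | 0.715 |
| 36 | 0.3 | 14 | ±3.0 | 0.033 | 0.712 | 0.727 |
| 36 | 0.5 | 21 | ±4.9 | 0.088 | 0.712 | 0.751 |
| 44 | 0.2 | 7 | ±1.2 | 0.006 | 0.796 | 0.798 |
| 44 | 0.3 | 14 | ±2.7 | 0.033 | 0.796 | 0.809 |
| 44 | 0.5 | 21 | ±4.4 | 0.088 | 0.796 | 0.831 |

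The largest gain is 0.751 − 0.712 = 0.039, about 4 points. The smallest is 0.798 − 0.796 = 0.002.

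**Step 4: is there bias or excess type I error?** In 20,000 simulated trials (36 per group, p = 0.3, g = 21, normal outcome, linear model) with no treatment effect, the mean estimate without the covariate was 0.03 days. Type I error was 0.048 without it and 0.049 with it. With a true 21-day effect, power was 0.702 without and 0.730 with. That gain of 2.8 points is slightly below the formula's 0.745 − 0.712 = 3.3 points for the same inputs.

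**Age.** The documents give nothing from which to size its effect, so none is calculated.

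**The case against.** Adjusting for the randomisation strata is a standard and valid choice, and any trial could be asked for one more covariate. Randomisation balances duration and age in expectation, and the standard error already allows for chance imbalance. All of this stands, and Step 4 bears it out. A reader might infer that the mix of delayed unions and non-unions distorts the primary result. The documents do not support that: even the largest 95% shift in the table, 4.9 days, is below one standard error (8.33 days at the same sample size).

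A reader might also infer that delayed unions are shown to heal faster after grafting. The Background says only: "However, some potential for a union probably exists, especially in nondisplaced fractures, otherwise this condition is associated with a transition into a persistent non-union". That is hedged, does not concern time to union after surgery, and is strongest for nondisplaced fractures. The trial's delayed unions must have displacement above 1 mm or comminution, so even the direction of a route effect is uncertain. Likewise, the risk-factor list concerns developing non-union, not healing time after reconstruction.

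Nor does the plan ignore duration, since it has a subgroup analysis at the same cut. That analysis asks whether the treatment effect differs by duration; it does not adjust the overall estimate. The dislocation covariate may absorb part of a route effect, but its cut is 2 mm while the entry criterion uses 1 mm or comminution, and it says nothing about age.

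Imputation models usually hold more variables than analysis models, so their presence there is not in itself a contradiction. Finally, a fuller covariate list could be left to an analysis plan that is not shown. Here, however, the protocol itself names the covariates of the primary model, and the point concerns that list.

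**Conclusion.** The point holds as a modest matter of precision and consistency. The protocol states why it adjusts, then omits two recorded baseline variables that it treats elsewhere as relevant to prognosis. The estimate remains unbiased and type I error is kept, as the linear-model simulation with a normal outcome shows. Under the assumed share (20–50%) and gap (7–21 days), the uncorrected chance shift has a 95% range of about 1 to 5 days either way against a 21-day target. Adjusting for duration would add between almost nothing and about 4 points of power. The larger gains would be welcome, because two-sided power with the stated SDs is 0.71 at 36 per group and reaches about 0.80 only if all 44 per group are analysed. If duration has little bearing on healing after grafting, the gain is close to zero. For age, the case rests on the protocol's own risk-factor list alone.

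**What to change.** In the Data analysis section, extend the covariate list of the primary model to the three strata plus duration since fracture (below versus above 6 months, or continuous) and age, fixed before outcome data are seen. This applies whichever form of time-to-union model is finally used. Keep the planned subgroup analysis by duration.

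Do not add a randomisation stratum. A fourth binary factor would make 2⁴ = 16 cells for 88 patients, or 5.5 per cell on average.

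The cost is one sentence and about two model parameters. The data are already collected at enrolment.
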